### Method of Analysis

We will use the STATA 15 statistical software for analysis. Chi-square test will be used to compare the difference in prevalence of anxiety, depression and other variables between the groups at baseline. We will evaluate for changes in proportion of those outcomes at baseline to the end of the study using paired McNemar test. We will use logistic regression to assess the factors at baseline related to development of physical symptoms, overall, and in the HCPs group alone. Data will be described using appropriate descriptive statistics.

We will collect information for potential confounding factors such as age, gender, education level, and health conditions from both HCPs and their controls and adjust for these in the analysis. For all validated tools, we will use appropriate and previously published cut-offs to categorize them. For example, for the primary end point of anxiety, we will use the cut-off related to moderate anxiety, but also do a sensitivity analysis using cut-off using “mild” anxiety definition. Similar and consistent strategy will be followed for other validated tools. We will perform logistic regression for binary outcomes, such as those listed in our primary and secondary outcomes, after adjusting for pre-defined confounders including age, gender, and years of education. The choice of these *a priori* confounder is based on the significant association that exists for most of the study outcomes. We have also adjusted for time since the self-identified peak of the pandemic as this will impact on outcomes such as anxiety and depression. However, for the outcome of developing COVID-19 infection and change in prevalence of COVID-19 infection, we will also adjust for pre-existing medical conditions.

We will also stratify HCPs according to their roles (doctors, nurses, pharmacists, healthcare assistants etc.), and will evaluate and compare the endpoints by respective roles. Comparison between HCPs from the United Kingdom and outside will be undertaken adjusting for the self-identified peak of the pandemic in that region. We also will assess whether the years of experience (as a categorical variable) has any impact on the measured outcomes.

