## Study Objectives

### Primary Objective

(1)To evaluate the prevalence of symptoms of anxiety and depression at the time of COVID-19 pandemic amongst HCPs in direct patient-facing roles, as compared to colleagues/participants in non-patient facing roles.(2)To determine the change in symptoms of anxiety and depression during the follow-up period amongst HCPs in direct patient-facing roles, as compared to colleagues/participants in non-patient facing roles.(3)To evaluate the change in proportion of those with suspected or confirmed COVID-19 during follow-up period amongst HCPs in direct patient-facing roles, as compared to colleagues/participants in non-patient facing roles.

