#### Study Time Points

The study questionnaire will be conducted at baseline, after 6-weeks and 4-months for follow-up. The COVID pandemic in the United Kingdom started in March 2020 and the initial survey therefore assesses the early phase (baseline) and the follow-up (after 6-weeks and 4-months) questionnaires assess the mid-term impact.

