### Endpoints

#### Primary Endpoints

(1)Prevalence of anxiety and/or depression at baseline.(2)Change in prevalence of combined anxiety and depression from baseline.(3)Change in proportion of those who report signs and symptoms, or evidence consistent with COVID-19 from baseline to the end of study.

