#### Physical Health

##### Evidence consistent with probable diagnosis of COVID-19

This is self-reported and is assessed through questions regarding the presence of symptoms with the presence of either a self-reported positive test, or self-isolation for 7 days or more.

Customized questions on symptoms of COVID-19, swab and antibody status and days of absence/sick leave taken and potential need for hospitalization.

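### Primary endpoint 3 measures COVID-19 as a change from baseline without removing earlier cases, and the paired McNemar test that appears to apply cannot make the between-group comparison of objective 3

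*Protocol article*

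**What the plan says.** All references are to the protocol article.

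- **Primary Objective (3):** "To evaluate the change in proportion of those with suspected or confirmed COVID-19 during follow-up period amongst HCPs in direct patient-facing roles", compared with colleagues or participants in non-patient-facing roles. This is a between-group question.
- **Primary Endpoints (3):** "Change in proportion of those who report signs and symptoms, or evidence consistent with COVID-19 from baseline to the end of study".
- **Case definition** (under Physical Health): "presence of symptoms with the presence of either a self-reported positive test, or self-isolation for 7 days or more". The article gives no reference period.
- **Method of Analysis, change over time:** "We will evaluate for changes in proportion of those outcomes at baseline to the end of the study using paired McNemar test". The preceding sentence speaks of anxiety, depression and other variables. COVID-19 is not named in either sentence.
- **Method of Analysis, regression:** logistic models are planned for binary outcomes, with this addition: "for the outcome of developing COVID-19 infection and change in prevalence of COVID-19 infection, we will also adjust for pre-existing medical conditions". A further model is described as follows: "We will use logistic regression to assess the factors at baseline related to development of physical symptoms, overall, and in the HCPs group alone". Neither is limited to participants free of COVID-19 at baseline.
- **Exclusion Criteria:** the only criterion concerns written English, so earlier COVID-19 does not exclude anyone.
- **Study Design and Study Time Points:** recruitment opened on 24 July 2020, just after the first peak, and "The COVID pandemic in the United Kingdom started in March 2020". Earlier cases at baseline are therefore to be expected.

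**The concern.** A change-from-baseline measure suits a state that comes and goes, such as anxiety. Objective 3 is about COVID-19 arising during follow-up, which is a matter of new cases among people who can still become one. A change in proportion mixes those new cases with how much infection each group already had at baseline.

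The group expected to be more exposed may well enter with more earlier cases. If so, its follow-up risk is understated relative to the controls, and a real excess in patient-facing HCPs could shrink, vanish or appear with the wrong sign. A McNemar test within each group would not repair this, because it asks only whether that group's own proportion moved.

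**Working it through.** **1. The plan's own figure for paired change.** The Sample Size section claims about 80% power for a 15-point change in 160 participants (those with anxiety or depression symptoms at baseline), for all primary and secondary objectives. McNemar power is approximately Phi((d√n - 1.96√pd) / √(pd - d²)), with d the change and pd the share of discordant pairs. The article does not give pd, so the figure cannot be confirmed.
- pd = 0.46 (assumed): (1.897 - 1.329)/0.661 = 0.86, power 0.80.
- Changes in one direction only, so pd = d = 0.15: (1.897 - 0.759)/0.357 = 3.19, power 0.999.

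The stated 80% thus fits an outcome with movement both ways, not one that can only rise.

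**2. Item read as *ever had COVID-19*.** Pairs can move only from no to yes. With b new cases and no reversals, the exact two-sided p is 2 × 0.5^b:
- b = 5: 0.0625
- b = 6: 0.031

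The uncorrected chi-square version equals b, so b = 4 already gives p = 0.0455. Six cases are 1.9% of 320 followed HCPs (800 × 60% × two-thirds, from Follow-up study) or 1.5% of the 400 in End of Study Definition. The binomial chance of at least six new cases, by the assumed share of the followed group who become new cases, is:

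| Group size | 2% | 3% | 5% | 10% |
|---|---|---|---|---|
| 400 | 0.81 | 0.98 | >0.999 | >0.999 |
| 80 | 0.005 | 0.03 | 0.21 | 0.82 |

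The direction is fixed. Significance is near-automatic only in the large group.

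**3. Group contrast under *ever*.** Change = (1 - prior) × risk among those still at risk. The documents give no rates, so all of these are assumed.

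| Prior (HCP vs control) | Risk (HCP vs control) | True ratio | Change in points | Ratio of changes |
|---|---|---|---|---|
| 20% vs 5% | 10% vs 8% | 1.25 | 0.80 × 10 = 8.0 vs 0.95 × 8 = 7.6 | 1.05 |
| 30% vs 5% | 10% vs 8% | 1.25 | 0.70 × 10 = 7.0 vs 7.6 | 0.92 |
| 20% vs 5% | 10% vs 10% | 1.00 | 8.0 vs 9.5 | 0.84 |

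With equal risks, prior infection from 20% vs 10% up to 40% vs 10% gives ratios from 0.80/0.90 = 0.89 down to 0.60/0.90 = 0.67. The direction reverses only if the true ratio lies below (1 - control prior)/(1 - HCP prior): 0.95/0.80 = 1.19 at 20% vs 5%, or 0.95/0.70 = 1.36 at 30% vs 5%.

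**4. Group contrast under *since the last survey*.** Take the first row of rates, assume no reinfection, and let the follow-up answers cover all time since baseline. Change = (1 - prior) × risk - prior:
- HCPs: 8.0 - 20.0 = -12.0 points
- controls: 7.6 - 5.0 = +2.6 points

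COVID-19 would appear to fall in the group with the higher risk in both periods.

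**The case against.** Several counter-arguments carry weight.

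- **McNemar is not tied to COVID-19 by name.** Its use for endpoint 3 is inferred from the reference back to earlier outcomes. That stands, but no other test of change is named and the endpoint is worded as a change in proportion.
- **A model for developing infection is planned.** This is close to an incidence analysis, and a reader who infers that the plan has none would be wrong. However, the same sentence also models change in prevalence, and no at-risk set is stated.
- **The item's time window may be in the questionnaire supplement, which is not shown.** A reader might infer that the outcome is necessarily one-way. The documents do not say so: a self-reported, symptom-based definition can revert under a period window. Both windows were therefore worked through, and neither removes the problem.
- **All groups share one schedule, and time since the self-identified peak is adjusted for.** A common schedule does not equalise earlier infection, and each group's own baseline proportion is what gets subtracted. The adjustment does not enter a McNemar test.
- **McNemar uses only discordant pairs.** Under *ever*, earlier cases leave its p-value unchanged. They dilute the estimated change and bias its comparison between groups.
- **An article condenses.** The item wording and risk set may be in the full protocol. The form of the endpoint and the test for change, however, are choices that the article states.

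**Conclusion.** The point holds in a limited form. Endpoint 3 subtracts baseline COVID-19 status, keeps earlier cases in the denominator, and appears to rely on a within-group test for a between-group objective. Under either reading of the item the group contrast is distorted when earlier infection differs between groups: in the example, a true ratio of 1.25 becomes 1.05, or becomes -12.0 vs +2.6 points.

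These sizes rest wholly on assumed rates, and the second also on no reinfection. Two stronger conclusions are tempting but not supported. One is that the test result is automatic: only its direction is, and only under *ever*, while in groups of about 80 significance is far from assured. The other is that the sign will reverse: under *ever* that needs a larger imbalance in earlier infection or a smaller true effect than in the main example.

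**What to change.** - Define endpoint 3 as a first suspected or confirmed COVID-19 episode, by the article's own case definition, between baseline and the 4-month survey, among participants who reported none at baseline. Count cases from both follow-up surveys.
- Compare Group 4 with Groups 5 and 6 by the adjusted logistic regression already planned for developing COVID-19 infection, restricted to that at-risk set.
- State that McNemar is not used for this endpoint.
- Report COVID-19 before baseline separately, by group. Secondary endpoint 7 already goes part of the way.

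**Cost:** wording only, since COVID-19 status is already collected at baseline. The analysis set shrinks and the interval widens slightly. With an assumed 20% prior infection, 320 followed HCPs become 320 × 0.80 = 256. Repeat episodes in earlier cases fall outside this endpoint.

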## Introduction

The United Kingdom and the rest of the world now face a pandemic caused by a novel coronavirus, severe acute respiratory syndrome coronavirus 2 (SARS-CoV2). At the time of writing 1st October 2020) there were more than 34 million confirmed cases worldwide with over 1,000,000 deaths^1^. Healthcare professionals (HCPs) are at higher risk of developing life-threatening infectious diseases through exposure to respiratory droplets, aerosols, and contact with patients’ blood or body fluids. This has also been demonstrated in previous epidemics such as the Ebola virus disease in 2014 and Severe Acute Respiratory Syndrome (SARS) a decade earlier, which were associated with very high fatality rates in HCPs (Styra et al., 2008; Forrester et al., 2014; Alfaraj et al., 2018). Whilst efforts to minimize the physical impact of infectious outbreaks take precedence, the potential mental health impact of such pandemics in the short-term and beyond should not be neglected (Barello et al., 2020; Galli et al., 2020; Siddiqui et al., 2021).

Previous studies conducted on the mental health impact of infectious outbreaks have found significant burden among healthcare workers and the general public. During the SARS outbreak, healthcare workers in a Beijing hospital who were quarantined, worked in a high-risk clinical setting or had family or friends infected with SARS, reported substantially more post-traumatic stress symptoms compared to those without (Xiang et al., 2020).

Increased exposure and unprecedented large-scale quarantine measures have a negative mental health impact on the public, in addition to the already tangible economic repercussions (Thompson, 2020; Weiss and Murdoch, 2020). Increased workload alongside a suboptimal working environment of inadequate personal protection equipment (PPE), risk of nosocomial transmission and constant changes in work structure can have detrimental effects on the mental wellbeing of HCPs. The need to isolate for fear of infecting friends and relatives results in loss of a social support network, further compromising the psychological resilience of HCPs.

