Several studies exploring mental health impact of the current COVID-19 pandemic and risk factors for this have since been performed (Kisely et al., 2020). Whilst some individual studies have suggested an increased anxiety and risk of mental health problems in HCPs compared to non-HCPs (Zhang et al., 2020), subsequent meta-analyses have found a similar prevalence of anxiety and depression between healthcare workers and healthy controls from the general public (Krishnamoorthy et al., 2020; Luo et al., 2020; Pappa et al., 2020).

This observation can, in part, be explained by the different roles of HCPs. A study by Lu et al. (2020) demonstrated higher levels of psychological distress in HCPs working in hospital, compared to administrative staff. Work-related risk factors including close contact with infected patients, level of work experience and organizational support provided have also been shown to impact the psychological effect of emerging virus outbreaks (Kisely et al., 2020). These effects may be more prominent in junior or trainee doctors likely due to having to work in unfamiliar environment, with disrupted training and variable supervision (Kisely et al., 2020).

Healthcare professionals work under different schedules, including regular office hours, shift work, and swing shifts. Shift work and stressful work-related situations have been linked to poor mental health (Torquati et al., 2019). There is an established body of literature that has demonstrated the prevalence among physicians of a range of sleep-related issues, substance use and mental health disorders (Mihailescu and Neiterman, 2019; Petrie et al., 2019). These problems increase the risk of burnout or errors on the job. In those with pre-existing mental health disorders, there may be increased psychosocial problems, an increased risk of suicidal behavior, increased alcohol, or other psychoactive substance use, or a more severe form of the viral illness (Possamai, 2007; Greenberg et al., 2020).

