### Secondary Objective

(1)To assess the impact of COVID-19 pandemic on symptoms of anxiety and depression and behavioral changes in HCPs in comparison to the non-HCPs at baseline and follow-up.(2)To assess the impact of COVID-19 related symptoms of anxiety and depression and behavioral changes on the subsequent physical wellbeing and absence from work due to illness.(3)To study the relationship of perceived stressors, such as PPE provision, work hours, future vaccine introduction, staffing levels and support at work, on the physical and mental health of HCPs.(4)To compare the differences in the prevalence of symptoms of anxiety and depression and behavioral changes, if any, by role and years of experience of HCPs.(5)To assess the impact of COVID-19 pandemic on the symptoms of anxiety and depression and behavioral changes of HCPs in the United Kingdom compared with HCPs in Europe, Asia, Africa, America, and Australasia.

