## Study Questionnaire and Dissemination

This will be achieved through a wide distribution of the electronic survey to HCPs and non-HCP controls. We will seek endorsement and support from professional societies and associations in the United Kingdom and other parts of the world to disseminate this widely. Distribution networks that will be considered include network email distribution lists and relevant social media platforms.

We expect to have a larger distribution of the questionnaire in the United Kingdom, but we are aiming at achieving an international cohort of participants. Within the United Kingdom, dissemination will be through different NHS Trusts, geographically distinct deaneries involving with overseeing medical training, scientific and medical societies and universities. On an international level we will involve international medical and allied health scientific societies and associations.

There will be an invitation to join the study including an explanation of the reasons of the survey. Any participant taking part in the survey based on the brief description of the study will be deemed to have consented for the study, and no other consent will be required. This cross-sectional survey will include basic information about the participant including demographics, living circumstances, education level and pre-existing physical and mental health conditions. It will also include questions regarding work experience and profession, work circumstances and exposure to COVID-19. Table 1 provides a summary of the aspects assessed and the tools used.

**TABLE 1 T1:** Study variables and respective assessment tools.

Variables	Assessment Tool

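### The covariates named for the model of later physical illness do not include COVID-19 contact at work or recruitment group, so the secondary objective 2 estimate is open to upward confounding of uncertain, possibly small, size

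*Protocol article*

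**What the plan says.** Secondary objective 2 asks how symptoms of anxiety and depression, and behavioural changes, bear "on the subsequent physical wellbeing and absence from work due to illness". The analysis that serves it is in Method of Analysis: "We will use logistic regression to assess the factors at baseline related to development of physical symptoms, overall, and in the HCPs group alone".

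The same section describes adjustment in three places:

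- Information will be collected on, and the analysis adjusted for, "potential confounding factors such as age, gender, education level, and health conditions from both HCPs and their controls".
- Logistic models for the binary outcomes adjust for age, gender and years of education as a priori confounders, a choice that "is based on the significant association that exists for most of the study outcomes". Time since the self-identified peak is added.
- One sentence deals with infection outcomes: "However, for the outcome of developing COVID-19 infection and change in prevalence of COVID-19 infection, we will also adjust for pre-existing medical conditions".

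Contact with COVID-19 patients and recruitment group (1, 2 or 3) appear in none of these. Contact is measured, however. Study Questionnaire and Dissemination says of the baseline survey: "It will also include questions regarding work experience and profession, work circumstances and exposure to COVID-19".

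**The concern.** A variable that raises both baseline distress and the later risk of illness creates an association between the two even if distress has no effect on illness. The protocol describes contact as such a variable. On illness, the Introduction says: "Healthcare professionals (HCPs) are at higher risk of developing life-threatening infectious diseases through exposure". On the mental toll of outbreaks, it says: "Work-related risk factors including close contact with infected patients, level of work experience and organizational support provided have also been shown to impact". In its Discussion section, the article expects direct patient-facing work to harm both psychological and physical wellbeing.

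The stated rule for choosing confounders favours variables associated with most outcomes. Such a rule can pass over a variable that matters mainly for infection. The one infection-specific addition is medical history, not exposure.

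At stake is how objective 2 is read. If anxious staff become ill more often partly because they see more COVID-19 patients, the result could be taken as evidence that distress itself leads to illness and absence. The article intends its findings to guide support for HCPs.

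**Working it through.** **1. The plan's own figures.** All tests are two-sided at 0.05, normal approximation with pooled null variance.

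- Baseline, 40% vs 30% with 800 vs 250: power 82.2%. The plan says just over 80%.
- Follow-up, 20% vs 32.3%: the article does not say which two groups it means. Reading them as the 160 HCPs with and the 240 without baseline anxiety/depression (400 − 160), power is 79.1%. The plan says 80%.

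Both reproduce closely, and neither is disputed. On this reading, 20% vs 32.3% is not a risk by contact, so using it that way below is a borrowing.

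**2. Does the HCP-only run remove contact?** No. Under Participant Selection, Group 1 are HCPs in direct contact with COVID-19 patients and Group 2 are HCPs who are not. Restricting to HCPs removes the non-HCP contrast but keeps both groups. The analysis by role is by profession and compares endpoints; it does not adjust for contact.

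**3. Size of the bias.** Take two contact strata and assume no effect of anxiety/depression on illness within either. Let w be the share with contact, a1 and a0 the prevalence of anxiety/depression with and without contact, and r1 and r0 the illness risks. With contact left out of the model:

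- risk if anxious/depressed = [w·a1·r1 + (1−w)·a0·r0] / [w·a1 + (1−w)·a0]
- risk if not = [w·(1−a1)·r1 + (1−w)·(1−a0)·r0] / [w·(1−a1) + (1−w)·(1−a0)]

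The true odds ratio (OR) is 1, so any departure from 1 is confounding.

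*Planning rates borrowed* (a = 40% vs 30%; r = 32.3% vs 20%):

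- Overall, 800 vs 250: (320×0.323 + 75×0.20)/395 = 0.2996, and (480×0.323 + 175×0.20)/655 = 0.2901. OR 1.05, difference 1.0 point.
- HCPs alone, 800 vs 125: (320×0.323 + 37.5×0.20)/357.5 = 0.3101, and (480×0.323 + 87.5×0.20)/567.5 = 0.3040. OR 1.03, difference 0.6 points.

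*Stronger links within HCPs, assumed and not in the documents* (half with high contact; a = 50% vs 30%):

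- r = 32.3% vs 20%: (0.25×0.323 + 0.15×0.20)/0.40 = 0.277, and (0.25×0.323 + 0.35×0.20)/0.60 = 0.251. OR 1.14, difference 2.6 points.
- r = 30% vs 10%: (0.25×0.30 + 0.15×0.10)/0.40 = 0.225, and (0.25×0.30 + 0.35×0.10)/0.60 = 0.183. OR 1.29, difference 4.2 points.

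**4. Effect on the test.** The probability of a significant result at 160 vs 240 with no true effect, against a nominal 5%:

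| Case | Spurious OR | Rejection rate |
|---|---|---|
| HCPs, planning rates | 1.03 | 5.2% |
| Overall, planning rates | 1.05 | 5.5% |
| HCPs, assumed, r 32.3% vs 20% | 1.14 | 9.0% |
| HCPs, assumed, r 30% vs 10% | 1.29 | 17.9% |

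For scale, the planned difference of 32.3% vs 20% is an OR of (0.323/0.677)/(0.20/0.80) = 1.91.

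**The case against.** **The lists are open.** Both covariate lists are introduced as examples, and the sentence on physical symptoms refers to baseline factors without listing them. Exposure to COVID-19 is a baseline factor and could enter the model. This stands in part: the article does not say that contact will go unadjusted, and a reader who infers that it has been ruled out goes too far. But the article calls its set pre-defined and a priori and names an infection-specific extra without naming contact. Having contact among the candidate predictors would not commit the analysis to adjusting the anxiety/depression estimate for it.

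**An article condenses the full protocol.** True, and an unlisted covariate would not by itself be a finding. The point here is about a set the article does fix and justify, judged against what it says elsewhere about contact.

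**The bias is negligible at the plan's rates.** This stands as far as it goes. The planning rates give ORs of only 1.03 to 1.05, and even those borrow a risk that the plan does not clearly give by contact. The larger values depend on assumed inputs.

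**Objective 3.** A reader might infer that the models for PPE provision, work hours and other stressors are confounded in the same way. The documents do not support that as firmly. Nowhere do they say that contact determines PPE provision or hours, the objective is worded as a relationship, and contact may lie on the pathway from longer hours to infection, where adjustment would remove part of the effect sought.

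**Conclusion.** The point holds for secondary objective 2. By the protocol's own account, patient contact worsens both distress and physical health; contact is collected; and the named adjustment set contains neither contact nor recruitment group. The estimate is open to confounding, and the bias is upward if both links run as the protocol expects.

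A reader might conclude that the objective 2 result will be materially wrong. The documents do not show that. The spurious OR is about 1.03 to 1.05 with borrowed planning rates and about 1.1 to 1.3 under the stronger links assumed within HCPs. All these values assume two contact strata, no true effect, and no further covariates that partly stand in for contact. The case for changing the plan rests on a clear direction of bias and a very cheap remedy, not on a demonstrated large error.

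**What to change.** Add a short statement to Method of Analysis:

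- **Objective 2:** in the models for later physical symptoms, COVID-19 and absence, pre-specify recruitment group (1, 2, 3) as a covariate in the overall run, and the baseline COVID-19 exposure/contact variable in both the overall and HCP-only runs, alongside the covariates already listed.
- **Objective 3 (physical outcomes):** report the stressor estimates with and without contact, and say that contact may lie partly on the pathway.
- **Primary objective 3:** leave contact as the exposure of interest and do not adjust for it.

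No new data collection is needed. The cost is a few model degrees of freedom and, for objective 3, a second set of estimates to report.

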## Definitions of Various Endpoints: How We Will Assess Them

### Psychological

#### Presence of Anxiety

The presence of anxiety is screened using the Generalized Anxiety Disorder-7 (GAD-7) assessment. This is a validated self-administered patient questionnaire used as a screening tool and severity measure for generalized anxiety disorder (GAD). The minimum score is 0 and maximum score 21. The following scoring system will be employed (Kroenke et al., 2001):

*Mild: 5–9; Moderate: 10–14; Severe: >15*.

A score of ≥10 has a sensitivity of 89% and specificity of 82% for GAD. The GAD-7 scoring tool has also been shown to have acceptable sensitivity and specificity for other types of anxiety disorders such as panic disorder, social phobia, and post-traumatic stress disorder (sensitivity 68% and specificity 88% with a cut off score of 10, for any anxiety disorder).

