#### Presence of Depression

The presence of depression is screened using the Patient Health Questionnaire-9 (PHQ-9). This is a validated nine-item questionnaire designed to screen for depression, often used in a primary care setting. A PHQ-9 score of ≥10 has an 88% sensitivity and specificity for major depression (Spitzer et al., 2006). The severity of depression is rated as follows:

None: 0–4; Mild: 5–9; Moderate: 10–14; Moderately severe: 15–19; Severe: 20–27.

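### Primary objective 2 asks about change in symptoms between groups, but every named test uses GAD-7 and PHQ-9 only as yes/no: consistent with the endpoint, but inefficient

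*Protocol article*

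**What the plan says.** Primary Objective, item 2, reads "To determine the change in symptoms of anxiety and depression during the follow-up period amongst HCPs in direct patient-facing roles", with colleagues or participants in non-patient-facing roles as the comparison. Primary Endpoints, item 2, turns this into "Change in prevalence of combined anxiety and depression from baseline".

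Both instruments give graded scores. For GAD-7, "The minimum score is 0 and maximum score 21"; the PHQ-9 severity bands run to 27. The PHQ-9 section also supports its usual threshold: "A PHQ-9 score of ≥10 has an 88% sensitivity and specificity for major depression".

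Method of Analysis fixes how the scores are used: "For all validated tools, we will use appropriate and previously published cut-offs to categorize them". The worked example is anxiety, where "we will use the cut-off related to moderate anxiety", and the sensitivity analysis repeats this at the mild threshold. The other tools are to be handled in the same way. Groups are compared at baseline by chi-square, change is tested "using paired McNemar test", and adjusted analyses use logistic regression for binary outcomes. No analysis of either scale as a score is named.

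**The concern.** There are two gaps between the objective and the named analyses.

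- **Symptoms become a threshold crossing.** At a cut-off of 10, a move from 9 to 10 counts as change and a move from 11 to 20 does not. Worsening or recovery on one side of the line is invisible. The mild threshold moves the line but leaves the outcome binary.
- **The comparison between groups is not named.** The objective asks for change in one group relative to another. McNemar's test asks whether a proportion changed within one group. Logistic regression could be set up to compare groups, but the text does not say how it would express a difference in change.

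The follow-up sample is where precision is shortest: Sample Size assumes half of the 800 HCPs continue. A null result for objective 2 could then reflect the cut-off rather than an absence of change.

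**Working it through.** **1. The plan's own figures.** Power = Φ{[|p1−p2| − 1.96·√(p̄(1−p̄)(1/n1+1/n2))] / √(p1(1−p1)/n1 + p2(1−p2)/n2)}.

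- Baseline, 40% vs 30%, 800 vs 250: p̄ = 395/1050 = 0.376. (0.100 − 0.0688)/0.0338 = 0.92, power 82.2%. The article says just over 80%.
- Follow-up, 32.3% vs 20%, 160 vs 240: (0.123 − 0.0865)/0.0451 = 0.81, power 79.1%. The article says 80%.
- Change of 15 points in n = 160: about 80% if some 45-47% of pairs are discordant. The article gives no discordance.

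The two between-group figures reproduce as binary calculations.

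**2. Assumptions for the comparison.** The documents give no SD and no baseline/follow-up correlation ρ. I assume a normal score with SD 1 and ρ from 0.3 to 0.7. Prevalences of 30% and 40% are the planning rates in Sample Size. The 400 is half of 800 HCPs, as stated there; 125 applies the same half to the 250 controls, which is my extension.

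**3. One time point.** Relative efficiency of the cut = φ(z)²/[p(1−p)].

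- p = 0.30: 0.3477²/0.21 = 0.576, loss 42%.
- p = 0.40: 0.3863²/0.24 = 0.622, loss 38%.

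With skewed (gamma) scores and a scale shift, at prevalences of 20-40%, the loss was 35-44%, so this result does not hinge on normality.

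**4. Difference in change between groups.** One group moves from 30% to 40% and the other stays at 30%. The matching score shift is z(0.40) − z(0.30) = 0.271 SD.

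- Binary: variance of one person's change = P(discordant) − (change in prevalence)². At ρ = 0.5 this is 0.316 − 0.010 = 0.306 in the shifting group and 0.286 in the other. SE = √(0.306/400 + 0.286/125) = 0.0553. 0.10/0.0553 = 1.81, power Φ(1.81 − 1.96) = 44%.
- Score: SE = √[(2 − 2ρ)(1/400 + 1/125)] = √0.0105 = 0.1025. 0.271/0.1025 = 2.645, power Φ(2.645 − 1.96) = 75%.
- Relative efficiency = (1.81/2.645)² = 0.47, loss 53%.

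| ρ | Binary power | Score power | Information lost |
|---|---|---|---|
| 0.3 | 38% | 61% | 45% |
| 0.5 | 44% | 75% | 53% |
| 0.7 | 54% | 93% | 63% |

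**5. If follow-up is lower.** Follow-up study expects 60% to agree and two-thirds of those to respond, so 40%: 320 vs 100. At ρ = 0.5 the powers are 37% and 66%.

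**The case against.** The strongest reply is that endpoint, test and sample size agree with one another. Endpoint 2 is a change in prevalence, McNemar and logistic regression suit a binary outcome, and the power was computed for binary outcomes. The proportion above a published screening threshold is also a natural target for a study meant to guide support for staff. All of this stands. A reader might infer that the primary analysis is invalid or the stated power wrong; the documents support neither. The mismatch lies between objective 2 and endpoint 2.

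A second reply is that a supportive score model belongs in an analysis plan that is not shown. That is partly fair: such a plan could add one, and the article does promise descriptive statistics, so one cannot say that the scores will never be analysed as scores. But the article is not silent. It categorises all validated tools and chooses a second cut-off as the sensitivity analysis, and that stated choice is open to comment.

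A third reply concerns the power comparison. The 30% and 40% rates are for depression and/or anxiety combined, which is not a single score. If both scales shift equally and correlate 0.5-0.8 (an assumption), the shift per scale is 0.25-0.26 SD. Score power at 400 vs 125 and ρ = 0.5 is then 68-73%, or 58-63% if two tests share alpha. The advantage over 44% shrinks but remains.

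**Conclusion.** The point holds as a matter of efficiency and of fit to the objective, not as an error. Objective 2 receives no named score analysis and no named between-group test of change. Under normality, dichotomising costs about 38-42% of the information in a single-time comparison at the planning rates, and about 45-63% in a between-group comparison of change at correlations of 0.3-0.7. It is tempting to quote one loss of about 40% for the follow-up analysis; that figure belongs to a single time point and understates the loss for change. All these sizes rest on an assumed score distribution and correlation, and the power pairs also on translating a composite rate into one score shift. They are illustrations, not properties of this study's data.

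**What to change.** Keep change in prevalence as the primary endpoint, with its cut-offs and tests unchanged. Pre-specify, as a supportive analysis of primary objective 2, one linear mixed model for the GAD-7 total and one for the PHQ-9 total. Each has group, time and group-by-time terms, uses the baseline, 6-week and 4-month waves, and is adjusted for the same confounders as the logistic models. The group-by-time term then answers the between-group question directly.

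The cost is two models on data already collected, with no change to endpoint or sample size. The downside is two additional results to report, labelled supportive. Rewording objective 2 as change in prevalence would align it with the endpoint, but would recover none of the lost information.
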